#### Allocation and concealment of allocation

After enrolment and pre-assessment (T0, Fig. 1), group allocation to the study or control group will be realised via minimisation. An external statistician, who is not part of the study team, will run the group allocation via an online minimisation-tool ‘Qminim’ [27]. Minimisation is a well-approved form of randomisation that minimises group differences in pre-defined characteristics while continuing trial enrolment. In order to achieve the best possible balance between the two study arms, group allocation will be performed according to the following factors: sex (double weighted), age, Mini-Mental Status-Examination (MMSE) [28] and Bayer instrumental Activities of Daily Living (B-ADL) [29]. Due to external enrolment in the trial, central randomisation by a person not involved in the study, and the blinding of all investigators during the whole trial, allocation concealment will be realised in the course of the trial.

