### Sample

Patients from three special DCU of the LVR-Hospital Cologne will be screened by two senior psychiatrists, who are not part of the study team, based on the following inclusion criteria: diagnosis of dementia according to ICD-10-criteria [19] and a minimum length of stay of one week before enrolment into the study, in order to help patients get familiarised to the new ward setting and to exclude delirium. Clinical exclusion of delirium is furthermore based on the validated German version of the Confusion-Assessment-Method, which is performed in all eligible patients [20, 21]. Patients must be able to perform the Timed Up and Go Test (TuG) [22]. Written consent of the patients’ legal guardian as well as from the patient is required. Patients will be excluded according to the following criteria: symptomatic, non-vascular or non-neurodegenerative dementia, no legal guardian, cardiac diseases denying exercise participation; and aggressive behaviour that prevents participation in groups.

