#### Outcome measures

All outcome measurements will be conducted by experienced assessors from nursing and medical staff, blinded to group allocation. Primary and secondary outcome variables are presented in Table 1.

**Table 1 Tab1:** Objectives and instrumental set-up of the trial

	Variable	Instrument
Primary objective	Behavioural and psychological symptoms (BPSD)	Alzheimer’s Disease Cooperative Study-Clinical Global Impression of Change [33]
Secondary objective	Dimensions of BPSD	Neuropsychiatric Inventory (NPI) [35]
		Cohen-Mansfield-Agitation-Inventory [36]
	Caregiver burden	NPI-caregiver-subscale [35]
	Application of antipsychotics	Chlorpromazine-equivalents [34]
	Application of benzodiazepine	Diazepam-equivalents [36]
	Motor behaviour	Body fixed motion sensor
	Saliva cortisol levels	Demeditec™ saliva kits [42]
	Neurotrophic factor levels	Brain-derived neurotrophic factor from blood-serum probes [44]

As the overall effect of our intervention on BPSD as rated by the ADCS-CGIC [24, 25] is the primary outcome, that is the measure on which we will focus.

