Secondary outcome measures include dimensions of BPSD rated by the Neuropsychiatric Inventory (NPI) [33] and the Cohen-Mansfield-Agitation-Inventory (CMAI) [34]. All psychopathometric assessments will be accomplished by blinded investigators, who are responsible for interviewing both the caregiver as well as the medical and nursing staff. Further secondary outcome variables include the assessment of caregiver burden via the NPI-caregiver-subscale [33] and the effects on the application of two categories of psychotropic medication: antipsychotics and benzodiazepines. The individual dosage per day of routine and pro-re-nata medication will be converted for antipsychotics to Chlorpromazine equivalents [35] and for benzodiazepines to Diazepam-equivalents [36, 37]. The patients’ motor behaviour will be assessed by an inertial body-fixed sensor system. Body postures will be detected in four periods of 72 consecutive hours (see Fig. 2), based upon accelerometer, gyroscope, and magnetoscope data. As recommended by Trost *et al.* [38], the sensor system will be placed at the nearest possible position to the body centre of mass, the lower back. In accordance to Hatfield *et al.* [39], diurnal saliva cortisol-levels will be assessed every four hours from 08:00 a.m. to 12:00 p.m. on two consecutive days at T0 and T1 with Demeditec™ saliva kits (Demeditec Diagnostics GmbH, Kiel, Germany) [40]. Analysis of saliva cortisol-levels will be carried out via an enzyme-linked immunosorbent assay (ELISA). In order to analyse the effects on brain-derived neurotrophic factor (BDNF), blood-samples will be taken on the first intervention day at 08:30 a.m., at 05:00 p.m. and for T1 at 08:30 a.m. These samples will be centrifuged, blood serum will be stored in a fridge by -40 °C and the ELISA analysis will be realised via R & D Systems™ (R&D Systems Inc., Minneapolis, USA) [41–43]. Adverse events are recorded and a potential relation to the intervention will be evaluated by a senior old age psychiatrist, who is not part of the study team.

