#### Analysis

The patients’ baseline characteristics in both groups will be compared via Chi-square test for categorical data, Wilcoxon rank test for non-parametric or non-normally distributed characteristics and *T*-test for continuous and normally distributed characteristics. Pre-post-outcome analysis within and between the groups will be realised per intention-to-treat analysis for the primary outcome variable via Friedman analysis of variance (ordinal characteristics) and analysis of variance for interval characteristics. The analysis of circadian rhythms in motor behaviour will be conducted according to Witting *et al.* [45] by calculating inter-daily stability, intra-daily variability and relative amplitude. Advanced time series analysis of the patients’ daily activity patterns will be developed in accordance with recent developments by Kirste *et al.* [46]. Analysis of the patients’ characteristics and outcome criteria will be realised using SPSS (version 22) and Matlab (version R2014b).

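### Minimisation leaves baseline BPSD severity and care unit to chance although both can be known at allocation; this costs precision and credibility but causes no bias

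*Protocol article*

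**What the plan says.** The section on allocation states when and how patients are assigned: "After enrolment and pre-assessment (T0, Fig. 1), group allocation to the study or control group will be realised via minimisation". It gives the purpose and then the list: "In order to achieve the best possible balance between the two study arms, group allocation will be performed according to the following factors", namely "sex (double weighted), age, Mini-Mental Status-Examination (MMSE) [28] and Bayer instrumental Activities of Daily Living (B-ADL) [29". No reason is given for the extra weight on sex.

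The Sample section names the source of patients: "Patients from three special DCU of the LVR-Hospital Cologne will be screened". Unit is not among the factors.

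Under Outcome measures, the target is BPSD: "As the overall effect of our intervention on BPSD as rated by the ADCS-CGIC [24, 25] is the primary outcome". Graded severity is measured by two other instruments: "Secondary outcome measures include dimensions of BPSD rated by the Neuropsychiatric Inventory (NPI) [33] and the Cohen-Mansfield-Agitation-Inventory (CMAI) [34". The Analysis section plans pre-post comparisons, so a T0 value of NPI and CMAI is implied. For the primary outcome it names the method: "per intention-to-treat analysis for the primary outcome variable via Friedman analysis of variance (ordinal characteristics". It names no covariate or stratum.

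**The concern.** Minimisation is most useful when it balances the characteristics that best predict the outcome. Here that is, on the face of it, how disturbed the patient is at T0: severity sets the room for improvement and the scope for regression to the mean. Patients are in hospital because of these symptoms, but the eligibility criteria set no severity band. The only behavioural limit is aggression that prevents taking part in groups. A T0 score should be in hand when each patient is allocated, so leaving it out saves nothing.

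Care unit raises a similar question. Ward medical and nursing staff are interviewed for the ratings, and routine and as-needed psychotropic doses are outcomes. Units could differ in both respects.

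At stake is a trial of 130 patients that ends with visibly unequal baseline severity, a less precise comparison, and a result that readers discount. A later analysis plan can adjust for this, but it cannot redo allocations already made.

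**Working it through.** **Inputs.** From Sample size: d = 0.5, 1:1 allocation, α = 0.05, power 0.80, 53 per group, 130 enrolled. From the allocation section: four factors with weights 2:1:1:1. From Sample: three units. The documents do not give the correlation of severity with the factors or with change, so both are assumed below.

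**The plan's own figure.** 53 per group reproduces with a one-sided Wilcoxon-Mann-Whitney calculation (efficiency 3/π, d = 0.5), with power 0.803. The sidedness is not stated; nothing below depends on it. Allocated per arm: 130/2 = 65. Since the primary analysis is by intention to treat, 65 is the main case and 53 the evaluable target.

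**Step 1: chance imbalance in an unbalanced covariate.** In units of the between-patient SD, the arm difference D has SD = √(2/n), and P(|D| > t) = 2[1 − Φ(t/SD)].

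| n per arm | SD of D | 95% range | P(>0.20) | P(>0.25) | P(>0.30) |
|---|---|---|---|---|---|
| 65 | √(2/65) = 0.175 | ±0.34 | 25% | 15% | 9% |
| 53 | √(2/53) = 0.194 | ±0.38 | 30% | 20% | 12% |

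**Step 2: do the four factors protect indirectly?** The minimisation was simulated (2,000 runs) with assumed two-level factors, a biased coin of 0.8, and a multiple correlation R of severity with the factors.

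| N | R | SD of D | P(>0.30) |
|---|---|---|---|
| 130 | 0 | 0.172 | 8.4% |
| 130 | 0.3 | 0.171 | 7.5% |
| 130 | 0.5 | 0.161 | 6.2% |
| 106 | 0 | 0.188 | 11.3% |
| 106 | 0.3 | 0.187 | 10.9% |
| 106 | 0.5 | 0.180 | 9.4% |

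They protect only a little. The mean of D was within 0.01 of zero throughout, so there is no systematic shift.

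**Step 3: what balancing severity would buy.** Severity was added as a two-level factor of weight 2, with R = 0.3. At N = 130 the SD of D falls from 0.171 to 0.111 and P(>0.30) from 7.5% to 0.6%. At N = 106 the SD falls from 0.187 to 0.123 and P(>0.30) from 10.9% to 1.5%.

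**Step 4: carry-over to the ADCS-CGIC.** With r the correlation between baseline severity and rated change, the shift in outcome SDs is r × D. For D = 0.25:

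- r = 0.1: 0.1 × 0.25 = 0.025, which is 0.025/0.5 = 5% of d.
- r = 0.3: 0.3 × 0.25 = 0.075, or 15% of d.
- r = 0.5: 0.5 × 0.25 = 0.125, or 25% of d.

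**Step 5: care unit.** With three units of equal size (assumed), some unit's share differs between arms by more than 10 percentage points in about 45% of simulated trials at N = 130 and about 50% at N = 106. It differs by more than 15 points in 16–18% and 23–25%. Adding unit as a factor was not simulated.

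**The case against.** The best defence is that nothing here is an error. Sex, age, cognition and daily function are ordinary choices, and simple randomisation with no factors would also be valid. The balance phrase states an aim, not a result. Chance imbalance has expectation zero and is already covered by the test's error rate. All of this stands, and it limits the point to efficiency and credibility.

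A reader might infer more than the documents support:

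- **That the primary comparison is biased.** It is not; see the simulated means.
- **That a 0.25 SD imbalance is half the planned effect.** The two figures are on different scales. One is baseline severity, the other a rating of change, and the conversion is r, which is not given.
- **That an imbalance would stay hidden because the primary instrument rates change.** T0 NPI and CMAI would reveal it and can serve as covariates.
- **That the double weight on sex harms balance on BPSD.** It does not in itself; it is only unexplained.
- **That the units differ in prescribing or usual care.** No text says so. They belong to one department, share the same two screening psychiatrists, and have one description of usual exercise therapy. A unit effect is an assumption.

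It can also be said that adjustment in the analysis would recover most of the benefit without touching allocation, and that an unseen analysis plan may already provide it. That is fair, and its absence from the article is not counted here. It does not remove the case for balancing: the factor list is fixed in this document and acts patient by patient, and visible balance also spares the result an argument that adjustment leaves open.

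**Conclusion.** The point holds as a cheap improvement, not as a flaw in validity. With severity unrelated to the four factors, there is roughly a one-in-seven chance (15%, n = 65) to one-in-five chance (20%, n = 53) that the arms differ by more than 0.25 SD in baseline severity. The existing factors lower this only slightly even at an assumed R of 0.5. The consequence for the ADCS-CGIC is modest at the assumed correlations of 0.1 to 0.5 (5% to 25% of d for such an imbalance). It is more direct for NPI and CMAI, whose own baselines are what would be unequal. The part on care unit rests on an assumed effect of unit on ratings and prescribing and is the weaker half.

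**What to change.** For all further allocations:

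1. Add T0 NPI total, in two or three prespecified bands, and care unit as minimisation factors.
2. Give NPI at least the weight of sex, and justify or drop the double weight on sex.
3. Record the date of the change and the number of patients already allocated.

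In the analysis plan, prespecify adjustment for baseline NPI, unit and the other minimisation factors. The primary outcome then needs an adjusted ordinal model, such as proportional odds, because a Friedman test takes no such covariates. This step also covers patients allocated under the present rule.

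The cost is a short amendment and a change of settings by the external statistician, with no new data. The documents do not say whether the online tool allows a change of factors in mid-trial; if it does not, the adjustment alone still recovers most of the benefit. The downsides are slightly looser balance on the existing factors and a documented rule change after recruitment began in April 2015.

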#### Sample characteristics

Baseline characteristics will be recorded within the geriatric assessment, carried out by nursing and medical staff members of the LVR-Hospital Cologne, who are not part of the study team. This basic assessment includes sex, age, body-mass-index, type of dementia, the MMSE [28], the clock draw test [30], assessment of the cognitive reserve capacity according to Stern [31], TuG [22], the 10-meter gait speed [32] and B-ADL [29].

#### Outcome measures

All outcome measurements will be conducted by experienced assessors from nursing and medical staff, blinded to group allocation. Primary and secondary outcome variables are presented in Table 1.

**Table 1 Tab1:** Objectives and instrumental set-up of the trial

	Variable	Instrument
Primary objective	Behavioural and psychological symptoms (BPSD)	Alzheimer’s Disease Cooperative Study-Clinical Global Impression of Change [33]
Secondary objective	Dimensions of BPSD	Neuropsychiatric Inventory (NPI) [35]
		Cohen-Mansfield-Agitation-Inventory [36]
	Caregiver burden	NPI-caregiver-subscale [35]
	Application of antipsychotics	Chlorpromazine-equivalents [34]
	Application of benzodiazepine	Diazepam-equivalents [36]
	Motor behaviour	Body fixed motion sensor
	Saliva cortisol levels	Demeditec™ saliva kits [42]
	Neurotrophic factor levels	Brain-derived neurotrophic factor from blood-serum probes [44]

As the overall effect of our intervention on BPSD as rated by the ADCS-CGIC [24, 25] is the primary outcome, that is the measure on which we will focus.

Secondary outcome measures include dimensions of BPSD rated by the Neuropsychiatric Inventory (NPI) [33] and the Cohen-Mansfield-Agitation-Inventory (CMAI) [34]. All psychopathometric assessments will be accomplished by blinded investigators, who are responsible for interviewing both the caregiver as well as the medical and nursing staff. Further secondary outcome variables include the assessment of caregiver burden via the NPI-caregiver-subscale [33] and the effects on the application of two categories of psychotropic medication: antipsychotics and benzodiazepines. The individual dosage per day of routine and pro-re-nata medication will be converted for antipsychotics to Chlorpromazine equivalents [35] and for benzodiazepines to Diazepam-equivalents [36, 37]. The patients’ motor behaviour will be assessed by an inertial body-fixed sensor system. Body postures will be detected in four periods of 72 consecutive hours (see Fig. 2), based upon accelerometer, gyroscope, and magnetoscope data. As recommended by Trost *et al.* [38], the sensor system will be placed at the nearest possible position to the body centre of mass, the lower back. In accordance to Hatfield *et al.* [39], diurnal saliva cortisol-levels will be assessed every four hours from 08:00 a.m. to 12:00 p.m. on two consecutive days at T0 and T1 with Demeditec™ saliva kits (Demeditec Diagnostics GmbH, Kiel, Germany) [40]. Analysis of saliva cortisol-levels will be carried out via an enzyme-linked immunosorbent assay (ELISA). In order to analyse the effects on brain-derived neurotrophic factor (BDNF), blood-samples will be taken on the first intervention day at 08:30 a.m., at 05:00 p.m. and for T1 at 08:30 a.m. These samples will be centrifuged, blood serum will be stored in a fridge by -40 °C and the ELISA analysis will be realised via R & D Systems™ (R&D Systems Inc., Minneapolis, USA) [41–43]. Adverse events are recorded and a potential relation to the intervention will be evaluated by a senior old age psychiatrist, who is not part of the study team.

**Fig. 2 Fig2:**

Schedule of body-fixed sensor assessment of patient motor behaviour. Legend: Four 72-h episodes at baseline (T0); at the beginning of the intervention (Int 0); at the end of the intervention (Int 1) and after the intervention (T1)

#### Intervention

TAU includes exercise therapy for 45 minutes twice weekly. Patients within the study group will receive a 2-week exercise programme. On 3 non-consecutive days of the week, the patients allocated to the study-group will be offered four exercise sessions a day (see Table 2). In order to ease the patients’ participation, the exercise instructor will see the patient on his ward and ask him to take part in an exercise session. If the patient refuses or is hindered for other reasons, the exercise instructor will, however, see the patient at the next scheduled exercise session (Table 2) and offer him further participation. After positive feedback, a single session will be held for a net time of 20 minutes. After one exercise session, there will be a rest period of one hour. This specific time schedule will be carried out four times on each intervention day. Due to the provision of recurrent rest-activity periods throughout a day, this activation programme is called *exercise-carrousel.* The patients will be allocated to three different exercise groups with a maximum of three patients per instructor. Two exercise sessions include endurance exercise on seated-ergometers for the upper and lower limb. Furthermore, two exercise sessions focusing on strengthening exercises with wrist- and ankle-worn weights will be carried out. The net exercise time of 20 minutes includes two minutes of warm-up at the beginning and two minutes of cool down at the end. An endurance-exercise-period of 16 minutes or alternatively six strengthening exercises will be carried out.

**Table 2 Tab2:** Exercise carrousel schedule for one intervention day

Time/Group	a.m.						p.m.						
	09:00	09:30	10:00	10:30	11:00	11:30	00:00 to 02:00	02:00	02:30	03:.00	03:30	04:00	04:30
Group 1	I			II			Lunch break	III			IV		
Group 2		I			II				III			IV	
Group 3			I			II				III			IV

Strengthening sessions include six standardised strengthening exercises for the lower limb with two to five kilogramme ankle-worn weights on both legs (sit-stand, knee-extension in sitting position, standing heel-raise, knee-curl in standing position, hip-abduction and hip-extension in standing position); for the upper limb with 1- to 2-kg wrist-worn weights on both arms (biceps-curl, extended shoulder-lift in sitting position, rowing in 90° shoulder-abduction, shoulder-lift and shoulder-abduction in standing, dips on arm rest while sit-stand).

These strengthening exercises will run in two sets of twelve repetitions each. The exercise load will be increased progressively after each intervention day in increments of 1 kg for the lower limb and a 0.5 kg for the upper limb. An increase in exercise load requires optimal exercise execution regarding both range of motion and scheduled repetitions. Endurance exercise sessions are conducted with a scheduled intensity of one watt per kilogramme of body weight in upper and lower limb exercises. If the exercise sessions a) are adequately executed and b) no serious complications occurred, the exercise load will be augmented up to 1.5 watt per kilogramme body weight. In accordance to Edwards *et al.* [44] exercise adherence will be recorded for each exercise session, and not only physical presence will be considered but also the degree to which the scheduled exercise session was completed. For participation to be rated as complete, more than 50 % of the scheduled exercise load regarding time, intensity and adequate repetitions is required.

The average participation rate of subjects in our pilot study was 120 min/week. For our RCT, we expect the same average participation duration for the intervention group. In order to receive a comparable level of social stimulation to the study group, the patients in our control group will be offered two 1-hour sessions of social interaction (table games) per week.

#### Analysis

The patients’ baseline characteristics in both groups will be compared via Chi-square test for categorical data, Wilcoxon rank test for non-parametric or non-normally distributed characteristics and *T*-test for continuous and normally distributed characteristics. Pre-post-outcome analysis within and between the groups will be realised per intention-to-treat analysis for the primary outcome variable via Friedman analysis of variance (ordinal characteristics) and analysis of variance for interval characteristics. The analysis of circadian rhythms in motor behaviour will be conducted according to Witting *et al.* [45] by calculating inter-daily stability, intra-daily variability and relative amplitude. Advanced time series analysis of the patients’ daily activity patterns will be developed in accordance with recent developments by Kirste *et al.* [46]. Analysis of the patients’ characteristics and outcome criteria will be realised using SPSS (version 22) and Matlab (version R2014b).

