**Methods/Design:**

A single-centre randomised controlled trial will be conducted in three special dementia care units of an old age psychiatry hospital. Enrolled patients will receive either a 2-week exercise programme, or a 2-week social stimulation programme in addition to usual care. Due to the provision of four day-structuring exercise-sessions in the course of an intervention day, the exercise programme for the study group is called *exercise-carrousel*. Baseline and post-intervention assessment for the primary outcome variable - the overall effects on behavioural and psychological symptoms - will be measured by the Alzheimer's disease Cooperative Study-Clinical Global Impression of Change. The following objectives are set up as secondary outcomes: dimensions of the behavioural and psychological symptoms of dementia (BPSD) and caregiver burden, routine and on-demand psychotropic medication, patients’ motor behaviour, diurnal cortisol-levels from saliva probes and brain-derived neurotrophic factor-levels from blood serum.

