### Objectives

The primary objective of this trial is to investigate the effects of a day-structuring exercise programme on BPSD in inpatient hospital dementia care. The promising results of our pilot-study regarding the feasibility and effects of the *exercise-carrousel* on BPSD in hospital old age psychiatry care, led to the following study-hypothesis:*The intervention group, carrying out a 2-day-structuring exercise intervention in addition to treatment as usual (TAU), is hypothesized to show reduced BPSD at follow-up. In contrast, the control group, receiving social stimulation in addition to TAU, is not expected to show such changes.*

In addition to investigating the putative effects of the day-structuring exercise on BPSD, the following secondary-endpoint parameters are investigated: caregiver burden, total dose and frequency of application of antipsychotic and sedative medication, circadian rhythms of motor behaviour, saliva cortisol-levels and brain-derived neurotrophic factor.

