### Sample size

The calculation of the sample size was performed via G*Power 3.1 [23], taking into account following parameters: a medium effect size (d = 0.5) for the primary objectives, the overall effects on BPSD measured by the Alzheimer’s Disease Cooperative Study-Clinical Global Impression of Change (ADCS-CGIC) [24, 25], from our pilot-study; a 1:1 allocation rate; two measurements; non-parametric analysis due to ordinal characteristics of the instruments assessing the primary objective; and an α-error of 0.05 and a power of 0.80 (1-ß-error) according to Cohen [26]. Based on this calculation, each group shall include 53 patients. The enrolment of 130 patients is planned, as a drop-out rate of 25 % is expected based on the experience from the pilot study.

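### The only test named for the ordinal primary outcome, Friedman analysis of variance, has no group factor and cannot deliver the between-group comparison that the Analysis section promises

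*Protocol article*

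**What the plan says.** All references are to the protocol article.

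- **Analysis.** The aim is stated as "Pre-post-outcome analysis within and between the groups will be realised per intention-to-treat analysis", and the method as "for the primary outcome variable via Friedman analysis of variance (ordinal characteristics) and analysis of variance for interval characteristics". The chi-square, Wilcoxon and t-tests in the same section are assigned to baseline characteristics only.
- **Sample size.** The calculation assumes "non-parametric analysis due to ordinal characteristics of the instruments assessing the primary objective", with two measurements, d = 0.5, 1:1 allocation, alpha 0.05 and power 0.80. It arrives at 53 per group. Sidedness is not given. Enrolment is 130, with 25% drop-out expected.
- **Outcome measures.** The primary outcome is fixed: "As the overall effect of our intervention on BPSD as rated by the ADCS-CGIC [24, 25] is the primary outcome". By its name the instrument is a Clinical Global Impression of Change.
- **Abstract, Methods/Design.** It announces "Baseline and post-intervention assessment for the primary outcome variable".
- **Objectives.** The hypothesis expects reduced symptoms in the exercise arm and adds: "In contrast, the control group, receiving social stimulation in addition to TAU, is not expected to show such changes".

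**The concern.** The primary question of a randomised trial is whether the arms differ. The outcome is declared ordinal, so the analysis-of-variance branch of the sentence, reserved for interval data, does not apply to it. That leaves Friedman, a test for related samples. It can show that patients changed over time, but not that exercise patients changed more than control patients.

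This matters in the present setting. Patients are admitted because their symptoms are exacerbated, and both arms receive usual care, so improvement in both arms is plausible. A test of time would then be significant without any exercise effect. The hypothesis sets an expected change in one arm beside no such change in the other. That wording makes it easy to read two separate within-arm results as if they were a comparison.

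A second problem concerns the data the test would use. A pre-post test needs a value at each time, and an instrument that rates change may supply only one.

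**Working it through.** **1. What Friedman tests with two measurements.** Each patient's two values are ranked 1 and 2, and ties contribute nothing. With a patients improved and b worsened, the tie-corrected statistic is (a − b)² / (a + b) on 1 degree of freedom. This is the sign test in chi-square form. The treatment label appears nowhere in it. It can be run on all patients pooled or in each arm separately, and neither use compares the arms.

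**2. Which test the stated sample size fits.** Inputs from Sample size: d = 0.5, alpha 0.05, power 0.80, 1:1. For a two-group Wilcoxon-Mann-Whitney test with the normal-parent efficiency 3/π:

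- effective size m = 53 × 3/π = 50.6 per group
- noncentrality 0.5 × √(50.6/2) = 2.515, with df = 2m − 2 = 99.2
- one-sided 0.05, critical t 1.660: power 0.803 (52 per group gives 0.796, so 53 is the smallest)
- two-sided 0.05, critical t 1.984: power 0.702

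Other candidates do not give 53:

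| Test | n for 80% power |
|---|---|
| Mann-Whitney, two-sided | 67 per group |
| t-test, two-sided | 64 per group |
| t-test, one-sided | 51 per group |
| Paired signed-rank at a standardised difference of 0.5, two-sided | 35 |

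The stated figure therefore matches a one-sided, between-arm rank test that the Analysis section does not name.

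With the expected drop-out, 130 × 0.75 = 97.5 patients are evaluable, taken here as 49 and 48. The same formula with unequal groups gives noncentrality 2.406 and two-sided power 0.66.

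**3. Illustration with no exercise effect.** Assumptions, none of them from the article: a change rating that is a rounded normal with SD 1, clipped to −3 to +3 (7 points); the same mean improvement in both arms; 49 and 48 patients; 5% level.

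| Shift in both arms | Pooled Friedman rejects | Significant in exercise arm only | Mann-Whitney between arms |
|---|---|---|---|
| 0.2 SD | 42% | 18% | about 5% |
| 0.3 SD | 75% | 25% | about 5% |
| 0.5 SD | 99% | 12% | about 5% |

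The opposite failure also occurs. If exercise improves by 0.25 SD and control worsens by 0.25 SD, pooled Friedman rejects in about 4% of trials and Mann-Whitney in about 63%.

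**4. The same check if there are two genuine scores.** Assumptions: a 7-category score at each time, pre-post correlation 0.5, 53 per arm. With equal improvement of 0.25 and 0.5 SD, pooled Friedman rejects in 60% and 99%. The exercise arm alone is significant in 23% and 11%. Mann-Whitney on the change stays near 5%. The conclusion does not depend on which reading of the instrument is correct.

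**5. Baseline value.** The instrument's name describes a rating of change. The Abstract speaks of a baseline assessment of the primary outcome, and Sample size of two measurements. The article does not describe the scoring. If the rating is purely one of change, there is nothing at baseline to pair with the later rating, and a pre-post test on it is undefined. If a separate severity rating is taken at baseline, the article should say so.

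**The case against.** The strongest reply is that the between-group aim is written into the Analysis section, so this is a misnamed test in a condensed article and a fuller analysis plan may put it right. The first part stands. A reader might infer that no comparison of the arms is planned, and the text does not support that. But the article does fix a method for the primary outcome, and that method cannot meet the aim. This is a wrong statement, not a detail left to another document.

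Four further inferences go too far.

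- **That the plan has a false-positive rate of 75%, or of 25%.** The article does not say that Friedman will be run pooled or arm by arm, nor that significance in one arm alone counts as success. The shifts and the 7-point scale are also assumptions. The rates illustrate what Friedman could do here; they are not properties of the plan.
- **That the primary outcome certainly has no baseline value.** The Abstract and Sample size sections say otherwise and the scoring is not given. Only a request to reconcile them is justified.
- **That Friedman rules out intention to treat because it needs complete pairs.** Imputation is compatible with it, missing-data rules are commonly left to the analysis plan, and a Mann-Whitney test on post-intervention ratings loses the same patients. This does not separate the two tests.
- **That the hypothesis omits any contrast.** It does set one arm against the other. The wording is loose, and correcting it is a small edit.

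**Conclusion.** The analysis is wrong as written. For the ordinal primary outcome the article promises a between-group comparison and names a test with no group factor. That conclusion follows from the definition of the test and needs no simulation. The possible damage is large under plausible conditions: with equal improvement of 0.2 to 0.5 SD in both arms and no exercise effect, a pooled Friedman test would reject in about 42% to 99% of trials, against about 5% for a between-arm rank test. These figures hold only under the assumptions listed above. The baseline-value point is conditional on how the ADCS-CGIC is scored.

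Correcting the test also exposes the unstated sidedness. The 53 per group supports 80% power for a Mann-Whitney test only if it is one-sided at 0.05.

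**What to change.** - **Primary analysis.** Name a between-arm comparison of the post-intervention ADCS-CGIC rating in all randomised patients. A Wilcoxon-Mann-Whitney test suffices. A proportional-odds model is an alternative that can adjust for the minimisation factors.
- **Hypothesis.** Word it as a difference between the arms, and report within-arm change descriptively only.
- **Instrument.** State whether the ADCS-CGIC yields one change rating or a rating at each time, and bring the Abstract and Sample size sections into line.
- **Sidedness and power.** State the sidedness and restate the power to match. For the Mann-Whitney test at d = 0.5, one-sided 0.05 keeps 0.80 at 53 per group. Two-sided 5% gives about 0.70 at 53 per group and about 0.66 with 49 and 48 evaluable.

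The cost is wording in the Analysis, Objectives and Sample size sections; no new data are needed. The downside is a less favourable stated power if the test is two-sided. Keeping 80% two-sided would take 67 evaluable patients per group, which is a recruitment decision and not a matter of wording.
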